**In vivo viral latency**

During primary infection, HIV disseminates to lymphoid and nonlymphoid tissue. It has been shown that, despite HAART in patients with no detectable viremia, HIV can be detected in cells of the CNS, genitourinary system, and lymphoid tissue associated with intestinal mucosa (Fierer DS, 2006; Galván SR, 2006; Blankson JN, 2006). One of the reasons why the virus is not eliminated from these sanctuaries could be the fact that antiretroviral drugs find it difficult to gain access (especially in the CNS) and also that infected cells escape the vigilance of the immune system. There is very little information on whether these reservoirs (sanctuaries) act as a source of residual replication in the presence of HAART or as pure reservoirs of latently integrated viruses.

From a clinical viewpoint, a small number of CD4+ memory cells are currently believed to represent the most important reservoir of HIV (Finzi et al., 1999). This reservoir has been calculated to be approximately 106 cells, in other words, there is 1 cell reservoir for every 106 resting CD4+ cells (Chun et al., 1997).

The therapeutic approach to viral latency requires viral reactivation in the presence of HAART (Yang QE, 2004), a selective attack with immunotoxins against latently infected cells (Brooks, et al., 2003), and intensification of HAART (Ramratnam et al., 2004), although this is far from being a reality in the treatment of AIDS.

Productive HIV infection in CD4+ cells is a complicated biological process that occurs when different cellular and viral events take place simultaneously. After the virus enters the host cell, the viral replication cycle will depend on cell activation status. Thus, infection of resting CD4+ cells gives way to incomplete viral reverse transcription, which represents a short period of viral latency with preintegrated HIV (Bukrinsky et al, 1991; Korin and Zack, 1998). If the cells are stimulated during the first 3 days after infection, the process of reverse transcription is completed and the viral cycle progresses to a productive infection (Namikawa et al., 1990). However, some of these infected cells return to a quiescent state (postintegration latency in memory cells) and represent one of the greatest problems for eradicating the virus from the body (Han et al., 2007).

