This reservoir is established during the earlier phases of the infection and is obviously favored by the high viremia and hyperactivation of the immune system. The biology of the memory cells themselves means that the half-life of this reservoir has been calculated to be 44.2 months; therefore, the complete eradication of the reservoir would need 73.4 years of HAART (Siliciano et al., 2003). Nevertheless, these calculations depend on the real nature of the viral reservoir. In all patients studied with optimally performing HAART (the viral load in plasma is maintained below 50 copies of RNA/mL for several years), low levels of viremia may be due to residual replication, release of viruses from the reservoir, or a combination of both. Whereas some authors defend the idea that the reactivated viruses from the reservoir do not contribute to its subsequent maintenance (Siliciano, 2006) and, therefore, intensification of HAART would not be effective at reducing the size of the reservoir, other authors have shown that there is a clear communication between residual replication and maintenance of the reservoir, as exchange of viral particles between both compartments has been reported (Chun et al., 2005). According to these authors, the inclusion of integrase inhibitors and CCR5 coreceptor inhibitors would be expected to have a considerable influence on the dynamics and maintenance of this viral reservoir. This is one of the main objectives of this project.

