# STATISTICAL ANALYSIS

This is an exploratory pilot study that is trying to prove a concept. Therefore, it is not possible to estimate the size of the sample necessary to demonstrate this. A treatment group of 10 patients has been considered necessary, based on data from previous studies on the same subject, which have used between 4 (Lehrman et al. Lancet 2005) and 11 (Chun et al. J Clin Invest. 2005) patients.

The longitudinal and cross-sectional analysis of the frequency data of infected cells will be carried out using random-effects regression models. In these models, the variable time will be introduced as an independent variable assuming linear kinetics. The frequencies of infected cells will be calculated using a parametric maximum likelihood method described elsewhere for limiting dilution experiments (Myers, L.E., McQuay, L.J. & Hollinger, F.B. Dilution assay statistics. J. Clin. Microb 1994; .32, 732–739) and will be expressed as infectious units per million (IUPM) of resting CD4 T cells. The gradient of the log10 reduction in IUPM will be estimated according to time from the start of therapy. This modelling process will be carried out in 2 approaches. In the first, 2 models will be made to estimate the gradients of log10 reduction in IUPM in the group of patients treated with the drug (n=10). Assuming linear reduction kinetics over time, the half-life will be calculated. The second approach will estimate a single model of the same characteristics as the previous ones but will include an interaction term between time and the treatment received. Given the design of the pilot study (concept), the statistical results will be reported as the estimations together with their standard errors without placing emphasis on the P values found. All the analyses will be carried out using STATA ver 9.0.

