**STUDY METHODS**

**LATENTLY HIV-1-INFECTED MEMORY T CELLS QUANTIFICATION**

Two baseline determinations (three months apart) will be performed to investigate the accuracy of the method and the stability of the reservoir. We carried out a previously described co-culture assay. Briefly, PBMC will be isolate from 300 ml of heparinized whole blood using Ficoll density gradient centrifugation (Lymphocytes Isolation Solution, Rafer, S.L Zaragoza, Spain). Resting CD4+ T cells (CD4+/HLA-DR-/CD25-) will be isolate and purified using magnetic beads according to the manufacturer’s recommendations (Miltenyi Biotec, S.L. Bergisch Gladbach, Germany). CD4+ T-cell purity greater than 99% with less than 0.4% activation will be confirmed by flow cytometry. The isolated resting CD4+ T cells will be plate in replicate limiting dilutions and co-culture with allogenic irradiated PBMC from seronegative donorsand phytohemaglutinin (PHA). The co-culture will be incubating with 5% of CO2 and 37ºC.

The activated cell culture will be fed once a week with PBMC from healthy donors after depletion of CD8+ T cells. On days 15 and 21, culture supernatants will tested for HIV-1 replication using the HIV-1 p24 antigen assay (Innogenetics Diagnostica Iberia, S.L Tarragona, Barcelona, Spain). Infected cell frequencies will be determine by the maximum likelihood method and expressed as infectious units per million (IUPM) resting CD4+ T cells. The accuracy of the measurement will depend on the number of replicates tested at each cell dilution.

RESIDUAL VIREMIA QUANTIFICATION

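### The log10 IUPM regression cannot use an assay in which every well is negative, and the protocol gives no rule for keeping such assays; if they drop out, the slope and half-life may be pulled towards no effect

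*Protocol*

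**What the plan says.** The Statistical Analysis section sets out two stages.

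- Stage one estimates the frequency of infected cells at each visit: "The frequencies of infected cells will be calculated using a parametric maximum likelihood method described elsewhere for limiting dilution experiments". The result is expressed as IUPM. The study methods in Annex IV repeat the maximum-likelihood step.
- Stage two is a random-effects regression in which "the variable time will be introduced as an independent variable assuming linear kinetics". The quantity of interest is on the log scale: "The gradient of the log10 reduction in IUPM will be estimated according to time from the start of therapy". A half-life follows from it: "Assuming linear reduction kinetics over time, the half-life will be calculated".

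For this assay, neither the Statistical Analysis section nor Annex IV gives a detection limit, a substitute value or a censoring rule. The number of cells and wells plated is also not given; Annex IV says only that "The accuracy of the measurement will depend on the number of replicates tested at each cell dilution". By contrast, Annex IV does state a detection threshold (0.3 copies/ml) for the single copy assay of residual viremia.

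**The concern.** The chosen estimator can return zero and the chosen outcome scale cannot represent zero. A visit with no positive well therefore cannot enter the regression as written; in practice its log becomes a missing value.

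Such visits are most likely where the reservoir is smallest, which means late on treatment in the patients who respond best. The loss is then caused by the outcome, and the values that remain at those visits are the higher ones. The fitted decline is too shallow and the half-life too long.

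This affects the primary endpoint. The protocol intends to report estimates with standard errors and to give little weight to P values, so the estimate is the main product of the study. In a proof-of-concept trial, attenuation could hide a real effect.

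**Working it through.** **Inputs from the protocol**

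- Reservoir frequency (In vivo viral latency): "there is 1 cell reservoir for every 106 resting CD4+ cells", read as 10^6 because the exponent was lost in the text. This is 1 IUPM.
- Natural decay: "the half-life of this reservoir has been calculated to be 44.2 months". Check of the protocol's own eradication figure: 44.2 x log2(10^6) / 12 = 44.2 x 19.93 / 12 = 73.4 years, as stated. This also supports the 10^6 reading.
- Ten patients; two baselines, then Months 3, 6, 9 and 12 on drug.
- Blood for the assay: 300 mL, with CD4 above 350 cells/mm3. That gives at least 300,000 mm3 x 350 = 105 million CD4+ cells before selection and losses.

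**Assumed, because the protocol does not give them:** cells plated per visit, the true effect, between-patient spread, and any starting reservoir other than 1 IUPM.

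**Step 1: why the estimate is zero.** Under the single-hit model the likelihood of an all-negative assay is exp(-f x total cells). It is largest at f = 0, and log10(0) is undefined.

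**Step 2: how often this happens.** P(all wells negative) = exp(-IUPM x millions of cells plated).

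| IUPM | 5M | 10M | 20M | 40M |
|---|---|---|---|---|
| 1 | 0.7% | <0.01% | <0.01% | <0.01% |
| 0.1 | 61% | 37% | 14% | 2% |
| 0.05 | 78% | 61% | 37% | 14% |

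At the protocol's own frequency the event is rare. After a 1-log fall from 1 IUPM it is common unless many cells are plated.

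**Step 3: effect on the slope if these visits are missing.** Simulation of 10 patients with visits from Baseline 1 to Month 12, 5-fold dilutions from 5 million cells in 2 or 4 wells per level, between-patient SD 0.4 log10, and a patient-intercept slope on log10 IUPM. Plated totals are (5 + 1 + 0.2 + 0.04) x 2 = 12.5M and x 4 = 25M. The true 12-month change is -1.0 log10. Ranges are across repeat runs of 150 to 200 simulated trials.

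| Median start | 12.5M | 25M |
|---|---|---|
| 1 IUPM | -0.89 to -0.90 | -0.97 to -0.99 |
| 0.3 IUPM | -0.64 to -0.66 | -0.81 to -0.82 |
| 0.1 IUPM | -0.40 to -0.42 | -0.56 to -0.59 |

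From 1 IUPM with 50M plated the result is -1.02. A model fitted to the well counts gave -1.01 to -1.08 in the settings of the table.

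As half-lives, 12 x log10(2) / |change|: the truth is 12 x 0.301 / 1.0 = 3.6 months; -0.90 gives 4.0; -0.65 gives 5.6; -0.82 gives 4.4.

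Smaller effects from 1 IUPM with 12.5M are barely distorted: -0.5 gives -0.48 and -0.3 gives -0.30. The natural decline, 12 / 44.2 x 0.301 = 0.08 log10 per year, gives -0.08.

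**Step 4: a second, separate simulation.** Wells of 1 million cells plus duplicate 5-fold dilutions, SD 0.5 log10, random-intercept regression, 120 runs per scenario, true half-life 3 months. The share of the true slope recovered with 5/10/20/40M plated was 72/85/95/99% from a median of 1 IUPM and 46/61/75/88% from 0.3 IUPM. A random-intercept complementary log-log model on the well counts, against a true -1.20, gave -1.20 (1 IUPM, 5M), -1.21 (0.3 IUPM, 20M) and -1.27 (0.3 IUPM, 5M, the sparsest case).

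**Step 5: substituting a constant.** With 12.5M plated, a median of 0.3 IUPM and a true change of -1.0, replacing zeros by 1/N, 0.5/N or 0.1/N (N = millions plated) gave -0.56, -0.72 and -1.10. The constant sets the answer.

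**The case against.** The best case for the plan has four parts.

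- **The protocol does not say zeros are dropped.** A reader might infer that it does. That is only the literal result of taking a log of zero. A statistical analysis plan that is not shown, or the published dilution method that the protocol cites, could supply a rule. This stands, and the point is worded conditionally for that reason. It does not remove the point, because the protocol itself fixes an estimator and a scale that are incompatible at zero, and substituting a constant is not a safe repair.
- **The large biases rest on assumptions.** Starting values of 0.3 and 0.1 IUPM are not in the protocol, nor is a target effect of -1.0 log10. At least 105 million CD4+ cells are available before losses, so generous plating is possible. From 1 IUPM the simulated slope varies between trials with an SD of 0.07 to 0.13 in the -1.0 cases, so a bias of about 0.1 or less does not stand out from sampling noise. This stands, and it limits the size.
- **The bias is conservative in an exploratory pilot.** True, and a reason to rate the point as should-fix. But a proof-of-concept study can also mislead by missing an effect.
- **Unequal assay precision.** A reader might also infer that replicates change with cell yield and that the standard errors ignore assay error. The documents support neither. Annex IV links accuracy to replicate number without saying that the number varies, the Statistical Analysis section does not specify equal weights, and the residual variance absorbs average assay error. No such claim is made here.

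**Conclusion.** The concern holds in conditional form. As written, the two-stage analysis has no place for an all-negative assay. If such assays are lost, the slope and half-life move towards no effect, most of all when a strong effect, a small starting reservoir and few plated cells coincide.

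For an assumed true change of -1.0 log10 over 12 months, the estimate is about -0.9 from 1 IUPM with 12.5 million cells, essentially unbiased from 1 IUPM with 25 million or more, and about -0.65 (12.5 million) to -0.8 (25 million) from an assumed 0.3 IUPM. At 1 IUPM with smaller effects the bias is negligible.

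The documents do not support saying that the primary result will be materially biased in every case: the cells plated are unstated, and the low starting reservoirs are assumptions. The point is a should-fix, to be settled before analysis.

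**What to change.** Replace the two stages with one model on the well counts: binomial outcome (wells positive out of wells tested at each dilution), complementary log-log link, offset equal to the log of cells per well, a random patient intercept and the same time terms. The time coefficient divided by ln(10) is the log10 IUPM slope. This model uses a single-hit dilution likelihood and keeps all-negative visits. Add a random slope only if it can be estimated with 10 patients; the simulations used patient intercepts only.

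Alternatively, keep the log10 regression and treat each all-negative visit as left-censored at that visit's detection limit, defined in advance from the cells plated (roughly 1/N IUPM for N million, so 1/12.5 = 0.08 IUPM at 12.5 million).

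Under either option, record wells positive, wells tested and cells per well at each dilution, and report the number of all-negative assays per visit.

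The cost is a change of analysis wording, recording of data that the assay already produces, and slightly more complex code. Whether the named software, STATA 9.0, fits the chosen model was not checked and should be confirmed. No extra patients, visits or blood are needed.

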**14. Study population and total number of patients**

Adult patients with HIV infection and a viral load that has been suppressed for a long period (less than 50 copies/mL for at least 2 years) while on antiretroviral therapy. The study will include 10 patients that maintain the habitual antiretroviral therapy combined with maraviroc.

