## **Study development**

Patients who fulfill the inclusion criteria will undergo the following procedures:

- Clinical history including duration of antiretroviral therapy and demonstrated period of undetectable viral load.
- Complete physical examination including height, weight, and temperature.
- Heart rate and systolic and diastolic blood pressure.
- Blood count, biochemistry, and urinalysis as described in section 8.3.2 of this protocol. Women will undergo a pregnancy test.
- Determination of viral load using ultrasensitive methods and CD4+ T lymphocyte count in blood samples.
- Determination of viral tropism.
- Measurement of the size of the reservoir of latent virus and its reactivation capacity.

Blood samples will be extracted by conventional phlebotomy on the dates set out in the study time line. The determinations will be carried out in the study center, with the exception of the determination of viral tropism and measurement of the size of the latent reservoir. For the former, samples will be sent to the Monogram® laboratories in the United States of America, as this is the only laboratory in the world approved for phenotyping coreceptors. For the latter, the samples will be taken in two laboratories: Infectious Diseases Laboratory from Hospital Ramón y Cajal and to the Molecular Immunobiology Laboratory of the Hospital General Universitario Gregorio Marañón (Dra. [name]) in Madrid.

After inclusion each patient receives, in addition to their usual medication, a CCR5 coreceptor antagonist entry inhibitor (maraviroc) in a dose of 150-600 mg every 12 hours according to technical data and previous treatment.

Treatment will be administered for at least 12 months. During this period, viral load will be measured using ultrasensitive methods, the CD4 count will be determined in peripheral blood, and the size of the reservoir of latent virus will be measured every 3 months after a blood extraction of 350 of total blood. After the intensification period with maraviroc and after drug suspension, patients will be following up during two additional visits according the study plan.

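### If the decay rate stays near the protocol's cited 44.2-month half-life, a reservoir half-life reported with a standard error will be unreliable; report the log10 slope with its interval and invert the limits

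*Protocol*

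**What the plan says.** Protocol section 11 (Statistical analysis) estimates the frequency of infected cells as IUPM by maximum likelihood. It models the log10 value with random-effects regression on time and estimates the gradient from the start of therapy. It continues: "Assuming linear reduction kinetics over time, the half-life will be calculated". Near the end of the paragraph it adds that "the statistical results will be reported as the estimations together with their standard errors", without emphasis on P values. Section 11 does not exempt the half-life from that reporting rule and does not say what is calculated when the slope is flat or upward.

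The design inputs are elsewhere in the protocol:

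- Synopsis item 14: "The study will include 10 patients that maintain the habitual antiretroviral therapy combined with maraviroc".
- Study development: during treatment "the size of the reservoir of latent virus will be measured every 3 months".
- Annex IV: "Two baseline determinations (three months apart) will be performed to investigate the accuracy of the method and the stability of the reservoir".
- Rationale, under In vivo viral latency: "the half-life of this reservoir has been calculated to be 44.2 months".

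**The concern.** A half-life is the reciprocal of an estimated slope. When the slope may lie within one or two standard errors of zero, its reciprocal is badly behaved. It grows without limit as the slope approaches zero, changes sign when the slope crosses zero, and has no finite sampling variance. Any standard error printed beside it would in practice be a first-order (delta-method) approximation, which is accurate only when the slope is many standard errors from zero. A symmetric interval built from it can include negative half-lives and miss the values the data actually allow.

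The wording also presumes a reduction. If the estimated slope is upward, the formula returns a negative half-life, which has no meaning as a rate of decay. A reader may well set the reported half-life against the 44.2 months in the rationale, and would do so with an error bar that misstates what the data can exclude.

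**Working it through.** **Is 44.2 months on the same scale as the planned slope?** The rationale says "This reservoir has been calculated to be approximately 106 cells" (read as 10^6, the superscript having been lost in the text) and that "the complete eradication of the reservoir would need 73.4 years of HAART". Log-linear decay from 10^6 cells to one cell takes log2(10^6) = 19.93 half-lives. Then 19.93 × 44.2 / 12 = 73.4 years, which reproduces the stated figure. The cited half-life is therefore exponential decay and converts directly to a log10 slope.

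**Implied rate of decline.** d = log10(2) / 44.2 = 0.30103 / 44.2 = 0.0068 log10 per month. Over 12 months this is 0.082 log10, a fall of about 17%.

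**Precision of the slope.** Measurements at months 0, 3, 6, 9 and 12 give Sxx = 36 + 9 + 0 + 9 + 36 = 90 per patient. With n = 10 and no between-patient variation in slope (an assumption that favours the plan), SE(d) = SD / √(90 × 10) = SD / 30. The residual SD is not in the documents, so 0.2, 0.3 and 0.5 log10 are assumed, with 0.1 as an optimistic case. The off-treatment visits at months 15 and 18 are left out because the slope is meant to describe decay on treatment.

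**Chance of a negative half-life.** P = Φ(−d / SE). The delta-method SE of the half-life is 44.2 × SE / d.

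| Assumed SD | SE of slope | d / SE | P(negative half-life) | SE of half-life, months |
|---|---|---|---|---|
| 0.1 | 0.0033 | 2.04 | 2% | 22 |
| 0.2 | 0.0067 | 1.02 | 15% | 43 |
| 0.3 | 0.0100 | 0.68 | 25% | 65 |
| 0.5 | 0.0167 | 0.41 | 34% | 108 |

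The chance that a 95% interval for the slope (±1.96 SE) reaches zero, so that the half-life has no finite upper limit, is Φ(1.96 − d / SE). This is 83%, 90% and 94% at SD 0.2, 0.3 and 0.5, and 47% at SD 0.1.

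**One worked report at SD 0.3, with the estimate equal to 0.0068.**
- As planned: half-life 44.2 months, SE 65.
- On the slope scale, with t on 9 df (2.262): 0.0068 ± 2.262 × 0.0100, that is, from a decline of 0.029 to a rise of 0.016 per month. Inverting the limits gives a half-life of 0.301 / 0.0294 = about 10 months at one end, then no decay, and a doubling time of 0.301 / 0.0158 = about 19 months at the other.

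**If the drug speeds the decay.** The same formula over SD 0.2 to 0.5 gives:

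| True half-life | Decline per month | P(negative half-life) |
|---|---|---|
| 24 months | 0.0125 | 3–23% |
| 12 months | 0.0251 | 0–7% |
| 6 months | 0.0502 | about 0% |

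**Sensitivity.**
- Putting the month −3 baseline into the slope gives Sxx = 157.5. The SE of the slope is then 0.0050, 0.0076 and 0.0126, and negative half-lives fall to 9%, 18% and 29%. At SD 0.3 the SE of the half-life is 49 months.
- Allowing a between-patient slope SD of 0.01 (simulated, months 0–12) gives 18%, 26% and 34% negative. At SD 0.3 the 5th to 95th percentile of the half-life runs from −173 to +194 months.
- Plausibility of the SD range: the theoretical error of a limiting-dilution estimate at 1 IUPM, assuming duplicate wells, six dilutions at 3- to 10-fold steps and a top input of 1 to 10 million cells, is 0.25 to 0.39 log10. The protocol does not give the layout, so this only shows that 0.2 to 0.5 is not extreme.

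**The case against.** The strongest reply is that the reporting sentence is general and closes a paragraph about regression gradients. It names no standard error for the half-life and no symmetric interval, and the handling of a derived quantity is commonly left to an SAP, which is not at hand. This has force: the point rests on a literal reading. But the protocol does fix two things, that a half-life is calculated presuming decline and that results carry standard errors, and nothing separates the half-life from the second.

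The gradient is also to be reported with its SE, so a careful reader could build the right interval. That limits the harm but does not make an SE on the half-life valid.

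Several stronger readings are tempting and not supported:

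- *That the half-life is the trial's main result.* The primary endpoint is reservoir size. The half-life appears in neither the objectives nor the endpoint, and section 11 plans no comparison with 44.2 months.
- *That the protocol expects a slope near zero.* The Rationale expects a reduction if the reservoir is dynamic, without giving its size. The section on in vivo latency reports both that view and the view that intensification would not shrink the reservoir. A slope near 0.0068 is thus one outcome the trial must be able to report, not its hypothesis.
- *That negative values are frequent whatever happens.* They are rare with SD 0.1 or a true half-life of 12 months and a precise assay.
- *That the half-life may be literally undefined.* An estimated slope of exactly zero has probability zero. The quantity that does not exist is the sampling variance of the reciprocal.

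Finally, an SE larger than its estimate warns the reader, and this is an exploratory pilot. Both points are fair. Yet with P values played down, estimates and standard errors carry the inference, so they need to be meaningful.

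**Conclusion.** The point holds in a limited form. Taken literally, section 11 attaches a standard error to a reciprocal that does not support one when decay is slow. At the cited 44.2 months, with 10 patients followed over months 0–12, the slope is between 0.4 and 1.0 standard errors from zero across the assumed SDs of 0.5 to 0.2, and 15% to 34% of trials would return a negative half-life. These figures rest on an assumed residual SD, no between-patient slope variation and little or no drug effect. They shrink quickly as any drug effect or assay precision grows. Because the half-life is secondary and the slope itself remains interpretable, the consequence is moderate: a misleading error bar on one derived number, not a failure of the primary analysis.

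**What to change.** In section 11, make the slope of log10 IUPM per month with a 95% t-based confidence interval the reported result. Give the half-life only by inverting the limits of that interval, with no standard error, and state that there is no finite upper limit when the interval includes zero. For context only, show the slope beside −0.0068 per month (decline negative), the value implied by the cited 44.2 months. This reporting works whatever the sign of the slope.

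The cost is one or two sentences and no new data. The half-life will look less precise, and in a slow-decay result it will often have only a lower limit.

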## **Primary objective**

To evaluate, by means of a controlled clinical trial, the effect of therapy with a CCR5 coreceptor antagonist (Maraviroc) on the cell reservoir of HIV-1 on patients taking HAART.

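### The planned time-by-treatment interaction is not identifiable as a between-patient term in this one-group trial, and no stated analysis separates a maraviroc effect from background reservoir decay

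*Protocol*

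**What the plan says.** The Statistical Analysis section sets out two approaches. The initial approach is described by saying that "2 models will be made to estimate the gradients of log10 reduction in IUPM in the group of patients treated with the drug (n=10"), followed by a half-life calculated on the assumption of linear kinetics. The second is a single model that "will include an interaction term between time and the treatment received". On the time axis it says: "The gradient of the log10 reduction in IUPM will be estimated according to time from the start of therapy". Treatment received is not defined. Results are to be given as estimates with standard errors, with little weight on P values.

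The design has one group. Synopsis item 14 states: "The study will include 10 patients that maintain the habitual antiretroviral therapy combined with maraviroc". Synopsis item 8 gives the control drug as not applicable, and sections 4.2 and 4.3 say the same of randomisation and of type of control. Yet the Primary objective (section 3.2) reads: "To evaluate, by means of a controlled clinical trial, the effect of therapy with a CCR5 coreceptor antagonist".

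The reservoir is also measured off maraviroc. The Study Plan has two baselines, which Annex IV places three months apart, and visits at Months 15 and 18. Laboratory determinations, which include reservoir size, are marked at all eight visits.

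On background decay, the rationale (In vivo viral latency) states that "the half-life of this reservoir has been calculated to be 44.2 months" and derives 73.4 years of therapy for eradication.

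**The concern.** Two models followed by one joint model with a treatment interaction is the usual layout for two groups: a slope for each, then a test of their difference. Here there is one group. If treatment received means what distinguishes one patient from another, it takes the same value for everyone and the interaction is the time variable over again.

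The slope that remains describes change while on maraviroc plus existing therapy. The primary objective asks for the effect of maraviroc. By the protocol's own account the reservoir shrinks slowly without the drug, so slope and drug effect differ by the background decay. The section does not say how to take that decay into account, although the trial collects some data that bear on it. This is the analysis of the primary endpoint, so the choice of contrast should be fixed before the data are seen.

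**Working it through.** **Inputs from the protocol.** n = 10, all on maraviroc; visits at t = -3, 0, 3, 6, 9, 12, 15 and 18 months from the start of drug (Study Plan; Annex IV for the three-month baseline interval); background half-life 44.2 months. **Assumed, not in the protocol:** residual SD per reservoir measurement of 0.3 log10 IUPM (range 0.2 to 0.4), and no variation in slope between patients.

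**1. The protocol's own figure.** Halving 10^6 cells down to one takes log2(10^6) half-lives: 44.2 × log2(10^6) / 12 = 73.4 years. This agrees with the stated 73.4, so the half-life is consistent within the document. (The cell count appears as 106 in the text; the superscript was lost in extraction.)

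**2. Can the interaction be estimated?** Take the fixed-effect columns [1, time, treatment, time × treatment].
- Treatment = 1 for every patient: rank 2 of 4. Treatment duplicates the intercept, and time × treatment duplicates time. Not estimable.
- Treatment coded by visit (off at both baselines and at Months 15 and 18, on at Months 3 to 12): rank 4 of 4. Estimable within patients.

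**3. Background decay contained in the single slope.**
- Per month: log10(2) / 44.2 = 0.0068 log10.
- Over 12 months: 12 × 0.00681 = 0.082 log10, or 1 - 0.5^(12/44.2) = 17%.

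**4. Precision of the on-drug slope alone.** For t = 0, 3, 6, 9, 12 the sum of squares about the mean is 90. The SE per 12 months is 12 × SD / sqrt(90 × 10) = 0.4 × SD, which gives 0.08, 0.12 and 0.16 log10 at SD 0.2, 0.3 and 0.4. The background decay is therefore 0.082/0.08 = 1.02, 0.082/0.12 = 0.68 and 0.082/0.16 = 0.51 standard errors.

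**5. Precision of a within-patient contrast.** Fit an intercept and three linear segments, X = [1, min(t,0), t limited to 0–12, max(t-12,0)]. For on-drug minus pre-drug slope, c'(X'X)^-1 c = 0.2302. The SE per 12 months is 12 × SD × sqrt(0.2302/10) = 1.82 × SD, which gives 0.36, 0.55 and 0.73 log10 at SD 0.2, 0.3 and 0.4.

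**6. Why not pool the off-drug periods?** With one common off-drug slope (regressors 1, t, and t limited to 0–12) the SE falls to 0.31 at SD 0.3, but the contrast is biased if the effect reverses after the drug stops. I put a true on-drug effect of -0.30 log10 over 12 months into the eight visits, with no noise:

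| Reversal by Month 18 | Pooled-off contrast | Separate slopes (on minus pre) |
| --- | --- | --- |
| none | -0.30 | -0.30 |
| half | -0.57 | -0.30 |
| full | -0.83 | -0.30 |

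Pooling would exaggerate the effect in just the case where the drug works reversibly.

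**The case against.** The best defence is that the protocol never says treatment received is a fixed property of the patient. With on/off coding by visit the interaction can be fitted, and the exact coding of a covariate is a detail often left to a statistical analysis plan. This stands as far as it goes: a reader might infer that no treatment-by-time term can be fitted in this trial because everyone takes maraviroc, and the visit schedule does not support that. But the section gives no sign of a time-varying term. Its time axis starts with therapy, it assigns the off-drug visits to no contrast, and two models for one group remain unexplained.

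A reader might also infer that the slope will be tested against zero and all decay credited to the drug. The text does not say so. It names no reference value and plays down P values, and the half-life it reports is on the same scale as 44.2 months. The gap is that this comparison is never stated.

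Third, the background decay is small beside the noise, between 0.51 and 1.02 standard errors under the assumed SDs, and this is an exploratory pilot. That limits the size of the problem. It does not make a constant covariate estimable, and when estimation is the stated aim the quantity estimated has to be identifiable.

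Last, controlled is an isolated word: the synopsis objective omits it, and the design sections are clear. A reader might conclude that the objective is out of reach. The fairer reading is that the word is wrong and the conclusion must be limited.

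**Conclusion.** The section is wrong as written. The interaction is not identifiable as a between-patient term, two models are announced for one group, and nothing stated separates a drug effect from a background fall of 0.082 log10 (17%) over 12 months. The rank result follows from the design alone, and the 17% from the protocol's half-life; neither needs an assumed SD. All the standard errors depend on the assumed residual SD and on equal slopes across patients; real variation in slope would make them larger.

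That the wording is left over from a two-group design is plausible but is an inference. The trial does hold within-patient information on the off-drug state, but at an SE of about 0.55 log10 per 12 months it can only support the on-drug estimate and cannot replace a control group. The 44.2-month figure is an outside benchmark with its own uncertainty: the rationale itself says that such calculations depend on what the reservoir really is.

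**What to change.** **Section 11.** Delete the reference to two models and the between-patient interaction. Specify one random-effects, piecewise-linear model of log10 IUPM with three separate slopes: pre-drug (Baseline 1 to Baseline 2), on-drug (first to last dose) and post-drug (to Month 18). Do not pool the pre-drug and post-drug slopes. Report:
- the on-drug slope and half-life with 95% confidence intervals, beside the 44.2-month figure treated as an uncertain external benchmark;
- the on-drug minus pre-drug slope as supportive, with its imprecision stated;
- the post-drug slope descriptively.

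**Section 3.2.** Replace the description of the trial as controlled with single-arm, uncontrolled pilot, and limit the conclusion to match.

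**Treatment duration.** Synopsis item 15 gives 12 months, while Study development (section 7.2) gives 12 months as a minimum. These must be reconciled, because whether Months 15 and 18 are off-drug depends on it.

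**Cost.** Protocol wording and a few lines of code, with no new visits or data. The price is a wide interval on the within-patient contrast and a more modest claim.
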